Eighty percent of certified nursing assistants (CNAs) have reported experiencing CRBs while providing mouth care [25]. These behaviors ranged from mild resistance (e.g. clenching mouths closed or turning the head away) to extreme resistance (e.g., hitting or kicking the CNA) [26]. CRBs were often triggered by the CNA performing mouth care instead of allowing the older adult to do so [27]. Other precipitants to CRBs during mouth care included caregivers attempting to forcefully insert the toothbrush or swab into residents' mouths without alerting them; lack of praise or encouragement; compound commands versus simple one-step commands; no smiling or positive facial cues from the caregiver; and attempting to provide mouth care without prompts or gestures[27]. These findings support the theoretical foundation of this study, that is, CRB is a fear-evoked response to caregivers' unintentionally threatening behavior during mouth care.

As discussed in detail in another publication [28], CRB is conceptualized as behavioral responses to a perceived threat. In other words, the older adult with dementia sees the caregiving actions as a form of assault. This conceptualization of CRB is based on the neurobiology of the limbic system. The limbic system is designed to detect threat and initiate protective fear responses of freeze, flight, or fight [29-31]. The primary structure is the amygdala, comprised of varied sets of nuclei: lateral, basal, basolateral, and basomedial[29]. These nuclei interface with other structures in the limbic system, primarily the hippocampus, as well as the brainstem[32]. In a healthy brain, the hippocampus and select areas of the cerebral cortex receive and process signals from the amygdala to provide awareness, context, and judgment to the threat perception and subsequent fear response[30,33]. When the brain, especially the cerebral cortices and hippocampus, is compromised by the pathology of dementia, the ability to apply context to the perceived threat deteriorates. As reasoning and perception become altered, persons with dementia may interpret non-threatening situations (such as a CNA attempting to help the elder with mouth care) as an actual assault[33,34].

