### Description of Usual Care

Usual mouth care is a challenging issue. For many persons who resist care, "usual" mouth care may mean NO mouth care[27]. Designing a study in which a potentially powerful intervention is compared to an absence of care would be meaningless. In order to have parity between the control and experimental groups, members of both will receive mouth care from interventionists from the research team. The difference will be that the control interventionists will NOT receive training in techniques designed to prevent and reduce CRB. Instead, the control interventionists will receive training separate from the experimental interventionists. That training will consist of best mouth care practices specific to older adults[36-40]. For consistency, both subjects in the control and experimental groups will receive the same mouth care supplies during the duration of the study: Biotene™ toothpaste (dentate); Biotene™ alcohol-free mouthwash (both); soft toothbrushes (dentate); denture brushes (dentures); interdentate sticks (dentate); denture cleansing paste (denture); and denture cups.

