The potential exists for the control interventionists to address CRBs in some way by virtue of their experiences or humanistic approaches to care. While this potential cannot be ethically eradicated, its possible influence on the results can be addressed by having the control and experimental interventionists complete a "Provision of Mouth Care Form" at the conclusion of each mouth care interface. The "Provision of Mouth Care Form" will have a group of forced-choice questions concerning the completion of mouth care. There will be one open-ended question that requires the interventionists to describe what, if any, activities he or she employed to provide mouth care. An open-ended question is preferable to listing strategies or techniques, because the listing of these items could unblind the interventionist and threaten the design of the study. The experimental interventionists would be trained to complete the form by writing specific threat reduction strategies taught to them during their training. The control interventionists would be instructed to simply complete the form. By having both control and experimental interventionists complete the same form, additional risks for cross-contamination are reduced.

The PD will conduct random observations of 10% of the mouth care sessions provided by the control interventionists. The PD will complete a checklist of care-resistant strategies taught to the experimental interventionists. If the control interventionist is successfully employing these strategies to reduce CRB, the control interventionist will be debriefed, compensated for unworked scheduled shifts, and removed from the study.

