A treatment fidelity checklist will be used by the PD to monitor delivery of the intervention. The checklist contains components of the MOUTh intervention protocol, followed by "yes" (properly perfomed), "no" (not properly performed or incorrectly omitted), or n/a (not applicable). Ten percent (10%) of the mouth care sessions between experimental interventionists and NH subjects will be randomly rated. Retraining of the experimental interventionist will occur if any component of the MOUTh intervention protocol is not properly followed or is omitted. Additionally, experimental interventionists will complete the same treatment fidelity checklist if the MOUTh intervention was not delivered according to protocol. The PI and PD will monitor receipt of the intervention using measures for subject participation in the protocol: intervention dose (duration of mouth care session) and frequency (number of times mouth care completed). These methods and measures will help the team to monitor and ensure the reliability of the MOUTh intervention, its delivery, and its receipt.

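### The project director's 10% session checks rate and correct best mouth care only in the experimental arm, so an OHAT difference (H2) could partly reflect supervised technique

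*Protocol article*

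**What the plan says.** All references are to the protocol article.

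- **Shared component.** Description of the MOUTh Intervention lists best mouth care practice as the first of three components. Description of Usual Care says control interventionists are trained in best mouth care for older adults and get no training in preventing or reducing CRB. The aim is stated: "In order to have parity between the control and experimental groups, members of both will receive mouth care from interventionists from the research team".
- **Experimental arm (Treatment Fidelity).** "Ten percent (10%) of the mouth care sessions between experimental interventionists and NH subjects will be randomly rated". The checklist holds MOUTh protocol components, each marked as properly performed, not properly performed or wrongly omitted, or not applicable. "Retraining of the experimental interventionist will occur if any component of the MOUTh intervention protocol is not properly followed or is omitted". Experimental interventionists also fill in the checklist themselves when a session departs from protocol.
- **Control arm (Randomization and Control of Cross-Contamination).** "The PD will conduct random observations of 10% of the mouth care sessions provided by the control interventionists". The content is then given: "The PD will complete a checklist of care-resistant strategies taught to the experimental interventionists". The consequence is also stated: a control interventionist found to be using those strategies with success is debriefed, paid for the shifts that are lost, and taken off the trial.

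**The concern.** The comparison is informative about threat reduction only if basic mouth care is delivered equally well in both arms. The plan gives one arm a feedback loop on that care (observe, score, retrain) and states none for the other. Technique can then be held up in the experimental arm while it drifts in the control arm.

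H2 is the hypothesis exposed. Its outcomes are oral cleanliness, gums, mucosa and lips, measured by the OHAT total, and these depend on how well the mouth is cleaned. If the arms differ on OHAT, the data could not separate better technique under supervision from less resistance under threat reduction. No control-arm technique scores would exist to settle the matter afterwards.

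**Working it through.** **1. The two checks side by side**

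| | Experimental | Control |
|---|---|---|
| Sessions observed | 10%, random | 10%, random |
| Content scored | MOUTh components, which include best mouth care | Strategies taught to the experimental arm |
| Trigger | Any component faulty or omitted | Successful use of those strategies |
| Action | Retraining | Debriefing and removal |
| Self-report of deviations on the checklist | Yes | Not stated |

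The sampling rate matches. Content, trigger and action do not.

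**2. Does anything else measure control technique?**

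- The Provision of Mouth Care Form is completed by interventionists in both arms. It covers completion and has one open question on activities used.
- Session duration (stopwatch) and completion (sessions out of 42) are recorded in both arms and enter the models. They show whether care was given and for how long, not how well.
- The CRB rater in the room scores the resident's behavior.
- OHAT assessors are blinded to assignment. That protects the measurement, but not against a real difference in cleaning.
- Table 1 lists mouth care per the MOUTh protocol for the control group as well. This conflicts with Description of Usual Care, and the two must be reconciled. It does not extend the fidelity rating, which Treatment Fidelity limits to experimental interventionists.

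None of these measures technique.

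**3. Sessions already observed**

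The plan's own figures reproduce: 60 / (1 − 0.25) = 80 recruited, and 60 × 42 = 2,520 observations.

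- All recruited, 40 per arm: 40 × 42 = 1,680 sessions; 10% = 168 per arm.
- After 25% attrition, 30 per arm: 30 × 42 = 1,260 sessions; 10% = 126 per arm.

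These counts show that the remedy needs no extra visits. They say nothing about the size of any bias.

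**4. Scale of the planned effect**

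Recruitment, Sample, Sample Size takes a standardized coefficient of 0.05 or larger for the group dummy, in the oral health models as well, and also considers 0.1. A 1:1 dummy has SD √(0.5 × 0.5) = 0.5, so:

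- 0.05 / 0.5 = 0.10 SD between arms
- 0.1 / 0.5 = 0.20 SD between arms

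**5. What a technique difference could do (assumed range)**

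The documents give no size for any drift. As an illustration, suppose threat reduction has no effect on OHAT and technique alone shifts OHAT by b SD in favor of MOUTh. Take one OHAT comparison, 30 per arm and two-sided 5%. The chance of a significant result favoring MOUTh is Φ(b√(30/2) − 1.96):

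| b (SD) | Chance |
|---|---|
| 0 | 0.025 |
| 0.1 | 0.058 |
| 0.2 | 0.118 |
| 0.3 | 0.212 |

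The planned three-level model will give different figures. The table conveys scale only.

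**The case against.** **Silence.** The control check is described under cross-contamination, and the article does not say it is all the PD records. Checklist items are often left to a manual. This has some force: if the full protocol already scores control technique, only the reporting by arm remains to be added. But the article states content, trigger and action for each arm, and they differ, so the asymmetry is not inferred from an omission alone. That the experimental checklist covers brushing or denture technique does rest on best mouth care being a named MOUTh component.

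**H2 compares a package with usual care.** Best mouth care belongs to the package, so one could say its supervision does too. However, usual care is defined here as the same best-practice care without CRB training. Supervision is not among MOUTh's three components, and the costing section excludes research and monitoring from intervention costs.

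**Stronger readings that a reader might infer, and that the documents do not support:**

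- *That H1 is biased because forceful control care goes uncorrected.* Background does name "caregivers attempting to forcefully insert the toothbrush or swab into residents' mouths without alerting them" as a CRB precipitant. It stands in a list with lack of praise and compound commands, and the list supports the threat theory. Nowhere is avoiding it classed as shared best mouth care. More CRB under care without threat-reduction training is largely the H1 contrast itself. Perfunctory control care could even lower CRB.
- *That control residents face unmonitored risk.* A CRB rater attends, resistance is recorded twice daily in both arms, and the PD observes 10% of control sessions.
- *That 3 hours of training against 1 makes control drift likelier.* The longer course also covers dementia, threat theory, and CRB categories and strategies. Time spent on mouth care itself may be equal.

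**Conclusion.** The point holds as a risk of performance bias in H2. Followed as written, the plan scores and corrects the shared mouth care component in one arm only, which sits badly with its own parity aim. If control technique drifts, the OHAT comparison would move in favor of MOUTh. Whether it drifts, and by how much, is unknown, so it would be wrong to say that H2 is tilted. The scale argument (0.10 SD for the smaller planned effect) shows only that a modest drift would not be negligible; the drift values used are assumptions. No sample size or error rate in the plan changes. This is a cheap improvement to fidelity monitoring and does not invalidate the design.

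**What to change.** 1. In the 10% observations already planned in both arms, have the PD score one identical set of technical best-mouth-care items, limited to what both groups are taught.
2. Apply the same retraining trigger for lapses in those items to control interventionists. Limit their retraining to content they have already been taught.
3. Keep the contamination checklist separate, with its present purpose.
4. Leave CRB precipitants, such as forceful insertion, out of the shared items and out of control retraining. Coaching control staff on these could amount to the CRB-prevention training that the design withholds.
5. Report shared-item scores by arm beside the OHAT result, so that readers can judge whether technique was balanced.

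Cost: a slightly longer PD checklist, occasional control retraining and a few lines of protocol text. No added visits, residents or analyses of the primary models.

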Days 1-7 Baseline Observations Phase	**Experimental and Control Group** Resistiveness to Care (RTC-r) OHAT Surveillance for acute infections Surveillance for psychoactive medications	Twice daily × 7 days Once, after Day 7's mouth care session Once on Day 7 for previous 7 days Once on Day 7 for previous 7 days

Intervention Phase Days 8-28	**Experimental Group** Mouth Care per MOUTh protocol RTC-r OHAT Surveillance for acute infections Surveillance for psychoactive medications **Control Group** Mouth Care per MOUTh protocol RTC-r OHAT Surveillance for acute infections Surveillance for psychoactive medications	Twice daily × 21 days Twice daily × 21 days Three times, once after Day 14's evening mouth care session, once after Day 21's evening mouth care session, and once after Day 28's evening mouth care session Three times, once on Days 14, 21, and 28 for preceding week Three times, once on Days 14, 21, and 28 for preceding week Twice daily × 21 days Twice daily × 21 days Three times, once after Day 14's evening mouth care session, once after Day 21's evening mouth care session, and once after Day 28's evening mouth care session Three times, once on Days 14, 21, and 28 for preceding week Three times, once on Days 14, 21, and 28 for preceding week

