### Instruments and Measures

The schedule for data collection is listed in Table 1 located at the end of the manuscript.

***Resistance to care ***is a dependent variable for specific aim #1 and hypothesis H1 and a mediating variable for specific aim #2 and hypothesis H2. It will be measured using a refinement of the Resistiveness to Care Scale, which was developed specifically for use with persons with dementia[54]. The original instrument listed 13 behaviors. Each behavior was rated according to duration and to intensity (mild, moderate, or extreme). The original instrument was designed to be used with videotapes; thus, each behavior was recorded once and the duration for all episodes was measured using time in categories (0 = none, 1-16 seconds = 1; 17-59 seconds = 2; 1-2 minutes = 3; more than 2 minutes = 4). The original RTC was developed and tested using 68 subjects at three sites (311 observations), with α = 0.82 and Kappa values ranging from 0.82 to 0.92[54].

In our pilot study, videotaping mouth care was problematic because of confined space issues (small bathrooms) and privacy concerns[35]. As noted in the pilot study,[35] the RTC was refined and tested for this study. The refinements included removing the duration component, measuring the intensity for each individual behavior, counting the frequency of each behavior within the intensity category, summing all episodes of CRB, and then standardizing the scores by dividing the sum with the duration of mouth care (in minutes) to obtain the rate of CRBs[35].

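### Removal of control interventionists depends partly on the H1 outcome, while the experimental arm has only a process-based retraining rule

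*Protocol article*

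**What the plan says.** **Control arm** (Randomization and Control of Cross-Contamination). "The PD will conduct random observations of 10% of the mouth care sessions provided by the control interventionists", using a checklist of the strategies taught to the experimental interventionists. The consequence is: "If the control interventionist is successfully employing these strategies to reduce CRB, the control interventionist will be debriefed". That person is also paid for shifts not worked and takes no further part in the trial. Just before this, the section accepts that control staff may ease CRB through their own experience or humane manner. It says that this cannot ethically be eliminated, and that its influence can be addressed by having staff in both arms complete the Provision of Mouth Care Form.

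**Experimental arm** (Treatment Fidelity). "Ten percent (10%) of the mouth care sessions between experimental interventionists and NH subjects will be randomly rated". The action is: "Retraining of the experimental interventionist will occur if any component of the MOUTh intervention protocol is not properly followed or is omitted".

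**Outcome** (Instruments and Measures). Resistance to care "is a dependent variable for specific aim #1 and hypothesis H1 and a mediating variable for specific aim #2 and hypothesis H2".

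**Control condition.** Description of Usual Care says that "the control interventionists will NOT receive training in techniques designed to prevent and reduce CRB". Table 1 (Methods/Design) has the entry "Control Group Mouth Care per MOUTh protocol".

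**The concern.** A rule to limit contamination needs to know one thing: whether a control interventionist is using techniques that belong to the other arm. This rule adds a second condition, that the techniques are working. CRB is what H1 compares, so who goes on delivering control care depends partly on the trial's own outcome.

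The condition exists in one arm only. It is judged by the project director, who must know the arm because the two arms are checked under different rules. Residents stay as randomized, but the group of people delivering control care is filtered. Even if the strategies had no effect at all, removing the users who happened to see low CRB and keeping those who saw high CRB would raise mean control CRB. At stake is an apparent MOUTh effect that partly reflects which control staff were left.

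**Working it through.** **1. The two rules side by side**

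| | Control arm | Experimental arm |
|---|---|---|
| Share of sessions checked | 10% | 10% |
| Trigger | Uses MOUTh strategies **and** does so successfully to reduce CRB | A protocol component omitted or not properly performed |
| Depends on CRB? | Yes, in part | No |
| Action | Debriefed and removed | Retrained |

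**2. The plan's figures** (Recruitment, Sample, Sample Size)

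- 12 × 5 = 60 evaluable; 60 / (1 − 0.25) = 80 recruited; 60 × 42 = 2,520 observations. These reproduce.
- Planned effect: a standardized coefficient of 0.05 on the group dummy. A balanced dummy has SD 0.5, so the difference in means is 0.05 / 0.5 = 0.10 outcome SD.

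**3. Size of the selection effect**

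The article gives no number of interventionists, no variance between them and no expected number of removals. The following inputs are therefore assumptions: between-interventionist SD τ = 0.1 to 0.3 outcome SDs, and a fraction f = 10% to 30% of control interventionists removed. If those removed are exactly the ones with the lowest CRB and are not replaced, the mean of the rest shifts by

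shift = τ · φ(z_f) / (1 − f),

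where z_f is the normal quantile at f. For f = 0.2: φ(−0.842) / 0.8 = 0.280 / 0.8 = 0.350, so τ = 0.2 gives 0.070.

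| τ | f = 10% | f = 20% | f = 30% |
|---|---|---|---|
| 0.1 | 0.019 | 0.035 | 0.050 |
| 0.2 | 0.039 | 0.070 | 0.099 |
| 0.3 | 0.058 | 0.105 | 0.149 |

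Halving these gives the coefficient scale: 0.010 to 0.075, against the planned 0.05. Only the two largest cells exceed the planned 0.10 SD; a third (0.099) is level with it.

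**4. What makes it smaller**

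- *Imperfect judgement.* If the director's judgement correlates 0.5 with true skill, every cell halves. The coefficient range becomes 0.005 to 0.037, below 0.05 throughout. Because removal also requires strategy use, those removed need not be the best of all control staff, which works the same way.
- *Replacement.* A simulation with no true effect assumed 10 interventionists and 30 residents per arm, 42 sessions, resident SD 0.5, perfect identification, and removed staff replaced at random:

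| τ | Removed | Spurious difference (SD) | False positives favouring MOUTh (nominal 2.5%) |
|---|---|---|---|
| 0.2 | 0% | −0.001 | 5.2% |
| 0.2 | 10% | 0.029 | 7.8% |
| 0.2 | 30% | 0.063 | 10.9% |
| 0.3 | 0% | 0.003 | 8.8% |
| 0.3 | 10% | 0.049 | 13.8% |
| 0.3 | 30% | 0.094 | 19.0% |

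  The excess over 2.5% with no removal comes from ignoring clustering by interventionist, which is a separate matter. Only the rise from that starting rate belongs to the removal rule.
- *Earlier sessions.* Sessions delivered before removal still count unless they are discarded. With replacement, if half of a removed person's sessions came first, the shift halves (for example 0.063 to about 0.03).

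**5. Comparison with a strategy-use trigger**

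If action does not depend on CRB and there is no true effect, the expected shift is 0. If the strategies do work, acting on their use restores the intended contrast, which is the legitimate purpose of the rule.

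**The case against.** The strongest defence is that this is a contamination rule and not an outcome rule. Off-protocol care is defined by a checklist. No resistance score or CRB threshold enters the decision. The wording can be read as competent use of strategies whose purpose is to reduce CRB. Each arm's rule then simply holds staff to their assigned condition. Removal also has a reason: the section avoids even listing the strategies on a form, for fear of unblinding interventionists, and correcting a control interventionist for using them would carry the same risk.

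Much of this stands, and it rules out several stronger readings that a reader might infer:

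- *Any control interventionist who lowers CRB is removed.* The text does not say so. One who calms residents by other means stays.
- *The experimental arm has the mirror-image outcome rule.* It does not. Retraining follows low fidelity, not poor CRB results.
- *Table 1 shows that off-protocol control care is undefined.* The checklist defines it. The table entry is a separate contradiction and no evidence of biased removal.
- *The rule alone would produce the planned effect.* That needs the upper corner of the assumptions: large differences between interventionists, many removals, near-perfect identification, no replacement and no earlier sessions counted.
- *No analysis could address it.* Residents stay randomized and nothing in the article discards their sessions. Removals can be reported, and sessions before and after them compared, although the sessions that removed staff would have delivered are lost.

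The benign reading does not dispose of the point. On its plain wording the trigger includes success in reducing CRB, and under the benign reading those words are unnecessary.

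**Conclusion.** The point holds in a limited form. Removal of control interventionists depends partly on the H1 outcome, in one arm only, on the judgement of someone who knows the arm. Any resulting selection is expected to favour MOUTh.

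Its size is unknown. Under the stated assumptions it runs from about 0.02 to 0.15 SD with perfect selection and no replacement, and is smaller otherwise, against a planned difference of about 0.10 SD. These are illustrations, not estimates, and removals may prove rare. The planned effect is small enough that a modest bias matters, and the correction is cheap.

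Separately, Table 1 and Description of Usual Care contradict each other on what the control arm receives.

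**What to change.** 1. Delete *successfully* and *to reduce CRB* from the trigger. Any action should rest only on strategy use recorded on the project director's checklist, against a threshold set in advance, whatever CRB is seen.
2. If the interventionist is kept, repeat only the standard control training and do not name the strategies. This respects the unblinding concern.
3. State that all residents and all sessions, including those delivered before any removal, stay in the as-randomized analysis.
4. Report removals and retraining by arm.
5. Run a contamination sensitivity analysis based on the project director's checklist. The Provision of Mouth Care Form is a weaker basis: experimental staff are trained to write down the strategies and control staff are not, so it captures them differently by arm.
6. Reconcile the control-arm entry in Table 1 with Description of Usual Care.

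The cost is a wording change plus a short table of provider actions. The downside is small. Repeating the control training may leave some contamination, which biases toward no effect. A trigger based on use alone may also lead to a few more actions on control staff.
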